### 1.3. Rationale and Goals

The hypothesis of the Ischemic Heart Disease Epitranscriptomics and Biomarkers (IHD-EPITRAN) study states that specific features of IHD are mirrored as epitranscriptomic modifications in the circulating blood RNAs. For example, these changes can manifest as alterations of m^6^A and A-to-I abundance or changes in their decoration patterns or loci within an RNA transcript (Figure 2). Such rationale is suggested by associations between the cellular and molecular processes governed by these modifications and the pathophysiology of IHD. Firstly, formation and dynamics of atherosclerotic plaques could contribute with epitranscriptomic signals into blood since they are the pathophysiological “hotspots” of IHD. They have characteristic features including active inflammatory cell proliferation, altered cellular and paracrine signaling microenvironments, and changes in the luminal presentation of blood cell response-modifying structures [57,58,59,60,61]. Secondly, the myocardium suffering from and responding to varying degrees of ischemia can either directly through e.g., shedding or production of RNA-packed extracellular vesicles (EVs), or priming and altering the patrolling blood cells’ responses contribute to epitranscriptomic cellular or cell-free RNA signature changes in blood. Thirdly, IHD promoting systemic responses, of which for example efflorescence of clonal hematopoiesis (CH) in bone marrow [62,63,64,65,66] and splenic hematopoiesis seeding proinflammatory monocytes [63,67,68] can be expected to alter blood epitranscriptomic signatures. Mechanistically, these postulations are suggested from notions that: (1) some leukocytes (1a) do exit the plaques [69], and (1b) oscillate between circulation and ischemic myocardium [70,71], (2) monocytosis has been independently associated with stable IHD and MI [72,73], (3) m^6^A has been shown to partake in dendritic cell (specialized monocytes) activation [74], (4) METTL3-mediated m^6^A-hypermethylation seems to act as a downstream elicitor of atherogenesis in vascular endothelium in response to disturbed flow and oscillatory shear stress [75], (5) the plaques, juxtaposed platelets, and ischemic myocardium are known to shed EVs to circulation encasing unique miRNAs [59,76,77,78,79,80,81], (6) miRNAs in such EVs have recently been shown to be epitranscriptomically modified [82], (7) epitranscriptomic and epigenetic regulators (7a) are often noted as CH driver mutations [83], and (7b) are pivotal for proliferation of hematopoietic stem cells (HSCs) [31,84,85,86,87,88]. Based on this rationale, the IHD-EPITRAN study aims to identify novel epitranscriptomic biomarkers and drug therapy targets for IHD from blood (Table 1).

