#### 2.3.3. Coronary Angiography, Computed Tomography Angiogram, SYNTAX Score

An invasive coronary angiography (ICA) will be performed for all participants in study cohorts I–II and for most in AVR control cohort III based on clinical details (mainly for those >50 years of age). ICA will be used to identify the precise site and quality of coronary thrombosis and to focus the PCI revascularization on the cohort I. On the other hand, for the cohort II, ICA will be performed to identify the main culprit segment(s) and to guide the upcoming CABG operation. Critically, based on a clinical risk stratification, either ICA or CCTA will be performed as a screening test to expose either obstructive or non-obstructive IHD, respectively, prior the AVR operation in the AVS control cohort III. All patients in the control cohort IV will undergo CCTA imaging.

While a zero Agatston coronary artery calcium score [12] from CCTA imaging will be required for inclusion to the IHD-EPITRAN study (all in cohort IV, some in III), a synergy between percutaneous coronary intervention (PCI) with Taxus and coronary artery bypass surgery (CABG) (SYNTAX) will be calculated from all ICA results, providing symptom-independent estimates of the complexity of IHD [93]. Moreover, the culprit segment, number, and types of stents or bypasses during PCI or CABG in cohorts I and II, respectively, will be recorded.

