#### 2.3.5. Study Blood Samples

While a set of collected blood samples will be stored directly by the study personnel, another set is stored to respective collaborative biobanks of each participating clinical center with partial sample-derived aliquot reservation. The non-biobank study blood samples will include TEMPUS^TM^ whole blood samples (3 mL × 5) and EDTA blood-derived (9 mL × 3) plasma aliquots. The biobank samples will include EDTA blood-derived (10 mL × 1) plasma and buffy coat aliquots as well as blood-derived (10 mL × 1) serum aliquots. In addition to the above-described set of biobank samples, if needed, a single 3 mL EDTA blood sample is collected for DNA extraction. The samples will be collected twice in study cohorts I–III and once in cohort IV (Figure 3).

The first blood samples for cohort I (acute STEMI phase) will be collected within 72 h after PCI, but the goal is within the first 24 h. While the IHD-EPITRAN blood samples will be prioritized for processing within 1 to 1.5 h, the processing time span for the biobank samples can be expected to extend up to 8 h due to practical restraints. A summary of the study samples, their general processing and principal analytical methods with corresponding goals pursued are provided in Figure 4.

Whole blood samples—Cellular RNA will be derived from the TEMPUS^TM^ blood sample tubes designed to preserve whole blood RNA against the otherwise rapid extracorporeal degradation. First, the acquired TEMPUS^TM^ blood samples will be vigorously shaken for 10 s and stored at <−70 °C until further processing. Second, the whole-blood total RNA will be isolated from the rest of the sample material according to the manufacturer’s instructions (e.g., TEMPUS^TM^ Spin RNA Isolation Kit, ThermoFisher, Waltham, MA, USA) before storage for further processing (Section 2.3.7).

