## 3. Expected Results

The IHD-EPITRAN study provides both quantitative and up-to single nucleotide in situ qualitative m^6^A and A-to-I focused epitranscriptomic datasets from whole blood, plasma, and RAA tissues (Section 2.3.8 and Section 2.3.9) from both meticulously characterized and prospectively recruited clinical cohorts representing IHD, AVS, and cardiac health (Section 2.2). Moreover, both MRM and untargeted proteomic profiles from plasma and snap-frozen RAA tissue, respectively, are acquired (Section 2.3.10) alongside comprehensive panels of plasma metabolite and non-metabolite surrogate CVD biomarkers (Section 2.3.5). Additionally, in situ histological landscapes of A-to-I editome and m^6^A governing enzyme expressions from clinical RAA tissue samples affected by both IHD pathophysiology and AVS pressure overload are produced (Section 2.3.9).

The controlled prospective cohort design of the study (Section 2.2, Figure 3) enables multiple clinically relevant aspects to be evaluated for the aforesaid datasets. For example, IHD vs. non-IHD distinctions, comparison of acute and chronic manifestations of IHD, therapy evaluation and long-term detection of IHD exacerbations, as well as newly arising IHD (Section 2.6) are both achievable and assessable regarding these datasets when referenced to the comprehensively recorded clinical metadata (Section 2.3.1, Section 2.3.2, Section 2.3.3 and Section 2.3.4). The arising key outcomes are listed in Table 3 and illustrated in Figure 5. Importantly, the study is expected to identify several IHD-specific candidate modified RNAs as well as possible IHD-associated (consensus) sequences that harbor epitranscriptomic alterations, as recently suggested from human failing hypertrophic myocardium [36]. Because RNA modifications other than m^6^A and A-to-I are to be quantitatively evaluated as well, the study results can help us to better understand also the other epitranscriptomic pathway contributions to IHD pathophysiology.

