**Study cohort I, patients with myocardial infarction revascularized with urgent PCI**	
Stent thrombosis, vasospastic coronary occlusion	This is IHD-focused study, myocardial infartions of other than atherothrombotic etiology are excluded
MI complications (*e.g., chordal rupture, aorthic disserction, acute heart failure, cardiogenic shock*)	To focus biomarker discovery to the IHD-induced infarction-specific epitranscriptomic alterations
Global ischemia on electrocardiogram	High rish of insufficient PCI and ischemia relievement

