**Study cohort IV, patients screened negative for IHD with coronary computed tomography**	
Any prior cardiovascular disease or medication currently or in history	As critical non-IHD controls, the aim is to also recruit patients that represent overall “cardiovascular health”

**Table 3 ijms-22-06630-t003:** Planned outcomes of the IHD-EPITRAN study. Outcome 1 and outcomes 2–5 encase inter- and intra-cohort comparisons, respectively. Morbidity parameters: Section 2.3.2. *A-to-I*, adenosine-to-inosine; *AVR*, aortic valve replacement (III); *AVS*, aortic valve stenosis; *CABG*, coronary artery bypass grafting (II); *CCTA*, coronary computed tomography angiogram (IV); *m^6^A*, N^6^-methyladenosine; *IR*, ischemia-reperfusion; *PCI*, percutaneous coronary intervention; *STEMI*, ST-elevation MI (I).

Primary	Secondary
1. Study sample m6A and A-to-I profiles from the recruitment stage associating with IHD and AVS pathophysiology 1.1. Acute IR controlled for stable ishcemia, pressure overload, and homeostasis (I vs. II-III-IV) 1.2. Stable ishcemia controlled for acute IR, pressure overload, and homeostasis (II vs. I-III-IV) 1.3. Acute IR controlled for homeostasis (I vs. IV) 1.4. Pressure overload controlled for acute IR, stable ishcemia, and hemeostasis (III vs. I-II-IV)	4. Changes in the study sample m^6^A and A-to-I profiles (Recruitment vs. 3-months) associating to 4.1 Therapy effects on Pathophysiology at 3-month follow-up 4.1.1. STEMI-PCI effects (Resolution and relievement acute IR, remodelingl I vs. I) 4.1.2. IHD-CABG effects (Relievement of stable ischemia, remodeling; II vs III) 4.1.3. AVS-AVR effects (Relievement of pressure overload, remodeling; III vs. III) 4.2 All-cause mortality during 3-month follow-up 4.3 Beneficial/adverse/no-response for therapy as measured via echocardiography at 3 months 4.4 Surrogate (non-)metabolite CVD biomarker levels at recruitment, 3 months, changes between
2. Study sample m^6^A and A-to-I profiles from the recruitment stage associating with 3-moth follow-up clinicial parmeters 2.1. Cardiovascular mortality 2.2 Cardiovascular morbidity 2.3. MACCE 2.4 Cardiovascular medication increases or reductions	5. study sample m^6^A and A-to-I profiles from the recruitment stage as in outcomes 4.2.–4.5.
3. Changes in the sample m^6^A and A-to-I profiles (recruitment vs. 3-months) as in outcome 2	6. Study sample quantitative alterations in other RNA modifications as in outcomes 1–5 (2.3.8.)

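### Primary outcome 1.3 is labelled acute ischemia-reperfusion, but cohort I versus cohort IV cannot separate it from established coronary disease, and Table 3 lists no direct I versus II contrast

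*Protocol article*

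**What the plan says.** Table 3 gives four primary inter-cohort contrasts at recruitment: I vs II-III-IV (1.1), II vs I-III-IV (1.2), I vs IV (1.3) and III vs I-II-IV (1.4). Two of them carry the acute IR label: "1.1. Acute IR controlled for stable ishcemia, pressure overload, and homeostasis (I vs. II-III-IV" and "1.3. Acute IR controlled for homeostasis (I vs. IV". Table 3 has no line for I vs II.

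Cohort membership is fixed in Table 2 and Sections 2.2 and 2.3.3. For cohort I, "myocardial infartions of other than atherothrombotic etiology are excluded", and another cohort I exclusion is justified as follows: "To focus biomarker discovery to the IHD-induced infarction-specific epitranscriptomic alterations". Cohort IV must have a CCTA negative for IHD and "a zero Agatston coronary artery calcium score". Table 2 also excludes from cohort IV anyone with past or present cardiovascular disease or medication.

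Section 1.3 names plaques first among the expected sources of the blood signal: "formation and dynamics of atherosclerotic plaques could contribute with epitranscriptomic signals into blood since they are the pathophysiological" hotspots of IHD. Section 3 says the design allows "comparison of acute and chronic manifestations of IHD".

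**The concern.** A contrast isolates acute IR only if its two groups are alike in everything else that is expected to move the outcome. In 1.3 they differ by design in two disease factors: the infarct with its reperfusion, and established coronary disease. The study's own hypothesis is that the second factor alters blood RNA modifications without any infarct. No covariate adjustment within I vs IV can separate the two, because one factor does not vary independently of the other across these cohorts.

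A modification raised equally in acute and stable IHD is an IHD marker. Under 1.3 it would be reported as a primary acute IR result. Secondary outcomes 6 to 9 are defined by reference to outcomes 1 to 5, so the same label would pass to the other modifications, the plasma biomarkers, the proteomics and the leukocyte profiles. Cohort II has coronary disease without the acute event and is the natural comparator, yet Table 3 does not set it directly against cohort I.

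**Working it through.** **Inputs, all from Section 2.4 unless noted.** FDR 0.05; 20,000 genes tested; 1,500 prognostic; mean count 10; dispersion 0.43; fold change 2; n = 44 for power 0.95, then fixed at 50 per cohort (also Section 2.2).

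**Step 1: reproduce the plan's figure.** The per-test level that gives FDR 0.05 at power 0.95 is

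α* = (0.95 × 1,500 × 0.05) / (18,500 × 0.95) = 0.00405, two-sided critical value 2.874.

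For a negative-binomial count with mean μ, the variance of the log mean in a group of n is (1/μ + 0.43)/n. Then

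n = (2.874 + 1.645)² × [(1/10 + 0.43) + (1/20 + 0.43)] / (ln 2)² = 42.9.

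Using the null variance instead gives 44.3. Power at n = 44 is 0.956. The stated 44 and 0.95 are reproduced and are not in dispute.

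**Step 2: a purely chronic signal.** Assume a transcript with mean 10 in cohorts III and IV and 10 × f in both I and II, so there is no acute effect. With n = 50 and f = 2:

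- I vs IV: difference ln 2 = 0.693, SE = √[(0.48 + 0.53)/50] = 0.142, z = 4.88. Flagged with probability Φ(4.88 − 2.87) = 0.98.
- Outcome 1.1 with II, III and IV pooled (mean (20 + 10 + 10)/3 = 13.33): difference ln(20/13.33) = 0.405, SE = √[0.48/50 + 0.505/150] = 0.114, z = 3.56. Flagged with probability 0.75 by formula, 0.74 by simulation.
- Outcome 1.1 against the equally weighted average of the three cohorts on the log scale: difference (2/3) × 0.693 = 0.462, SE = √[0.48/50 + (0.48 + 0.53 + 0.53)/(9 × 50)] = 0.114, z = 4.05. Flagged with probability 0.88.
- I vs II: equal means, so flagged at about the per-test level, 0.004.
- Outcome 1.1 read as an intersection (I must differ from each of II, III and IV): about 0.003, because it cannot exceed the I vs II rate.

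**Step 3: range over the assumed fold change, n = 50.**

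| Assumed chronic fold change | I vs IV | I vs pooled II-III-IV | I vs average of II, III, IV | I vs II |
|---|---|---|---|---|
| 2 | 0.98 | 0.74 | 0.88 | about 0.004 |
| 1.5 | 0.48 | 0.24 | 0.30 | about 0.004 |
| 1.25 | 0.09 | 0.05 | 0.06 | about 0.004 |

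**Step 4: can the planned size support I vs II?** At the plan's inputs and n = 50, any two-cohort contrast with a true fold change of 2 has power of about 0.98, before any extra multiplicity adjustment across contrasts.

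**The case against.** The strongest reply is that outcome 1.1 stands ahead of 1.3 and names control for stable ischemia. The Figure 5 caption calls the four-partite scheme preferred, describes it as Venn-based, and says that pairwise comparisons carry the least adjustment. On an intersection reading, I vs II is already a component of 1.1 and a purely chronic signal is screened out. A reader might infer that the primary outcomes leave chronic disease uncontrolled altogether; the article does not support that. What stands against the reply is that the article does not say whether II-III-IV is an intersection, a pool or an average, and only the first protects. In addition, 1.3 remains a separate primary outcome with its own acute IR label. Saying that it is controlled for homeostasis discloses what is controlled, but does not make the label right for what remains.

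Other stronger readings also go too far:

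- *I vs II is planned nowhere.* The Figure 5C image is not available and its caption speaks of pairwise comparisons in the plural. The absence is established for Table 3 only. For the same reason it cannot be said that I vs IV is the contrast left if another cohort is delayed.
- *Cohort IV is free of plaque.* The text requires a zero calcium score and a CCTA negative for IHD, no more.
- *Cohort II is a full match.* Cohort I blood "will be collected within 72 h after PCI, but the goal is within the first 24 h", whereas cohort II is recruited at the preoperative visit. Procedure, treatment and sampling time still differ.
- *Nothing else separates acute from chronic.* Secondary outcome 4.1.1 compares cohort I with itself at 3 months. It helps, but it is secondary and mixes resolution with remodeling.

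It is also fair that the 0.98 is the study's own power applied to an assumed chronic signal. It shows what 1.3 would do if such a signal exists, not that one does.

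**Conclusion.** The point holds for outcome 1.3 taken alone: its acute IR label claims more than I vs IV can show. It extends to 1.1 only on a pooled or averaged reading, which the article neither adopts nor rules out. For a chronic-only transcript, the probability of being called acute IR in 1.3 is about 0.98, 0.48 and 0.09 at fold changes of 2, 1.5 and 1.25 with 50 per cohort, against about 0.004 in I vs II. These figures rest on the plan's sizing inputs and on assumed fold changes. The sample size is sound on its own inputs. This should be changed: it affects what a primary finding may be called, and the correction is cheap.

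**What to change.** In Table 3, with Figure 5 brought into line:

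1. Relabel 1.3 as acute IHD (acute IR plus underlying coronary disease) versus homeostasis.
2. List I vs II at recruitment, either as its own contrast or as a required component of 1.1, and state how II-III-IV is combined in 1.1.
3. Call a modification acute-IR-associated only if it also differs in I vs II in the same direction. Report other I vs IV hits as acute-IHD-associated.
4. State that I vs II still differs in procedure, treatment and sampling time.

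The cost is wording plus one analysis on samples already planned, with no extra patients or assays. The downsides are one more contrast in the multiplicity family and fewer hits labelled acute IR.

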### 2.2. Study Groups, Recruitment and Exclusion Criteria

The IHD-EPITRAN study will recruit 50 patients in each of the four study groups to reach its first subgoal of a total of 200 patients. However, the study is expected to continue after the completion of this first phase to increase cohort sizes and study power over time (www.ihd-epitran.com, accessed on 24 May 2021).

The first study cohort (I) consists of patients admitted to the cardiac care unit (CCU) and recruited within 72 h of revascularization via percutaneous coronary intervention (PCI) for MI with ST-elevations (STEMI). The second study cohort (II) consists of patients with chronic coronary syndrome (CCS, typically of category 1: suspected chronic IHD due to anginal symptoms [12]). These are patients with persistent IHD symptoms scheduled to undergo elective coronary artery bypass grafting (CABG) operations. The third study cohort (III) consists of non-IHD patients undergoing aortic valve replacement surgery (AVR) for aortic valve stenosis (AVS). The fourth study cohort (IV) consists of patients diagnosed as negative for IHD with coronary artery computerized tomography angiography (CCTA) imaging. The former two cohorts (I-II) represent patients with IHD while the latter two cohorts (III and IV) represent non-IHD control patients. A chronologic and cross-sectional summary of the study cohorts is provided in Figure 3.

While patients in cohort I will be recruited during the hospitalization period, the cohorts II and III will be recruited during the preoperative visit. Patients in cohort IV will be either (1) preselected based on received referrals by the outpatient-treating physicians to CCTA imaging or (2) contacted after CCTA imaging if it has been negative for IHD within the last 3 months and exclusion criteria are met (Table 2).

All recruited patients will be invited for an echocardiography visit (Section 2.3.4). The study information sheets will be sent well beforehand to ensure familiarization of the study for the candidate participants when possible (cohorts II and IV) and delivered as soon as practical according to the clinical situation in CCU for patients in cohort I. Patients aged 18–80 years and meeting the cohort-specific descriptions are eligible for participation in the study. The exclusion criteria and their rationales are presented in detail in Table 2.

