#### 2.3.4. Echocardiography, 3-Month Control Visit, and Follow-Up Period

As the development of more sophisticated echocardiographic techniques has revolutionized the field of cardiology and cardiac surgery by offering relevant dynamic insights to both cardiac anatomy and function, IHD-EPITRAN will assess all participants in all cohorts with transthoracic echocardiography (TTE). Critically, the non-IHD control patients in cohort IV will also undergo TTE recording. In this way, valuable functional reference values are obtained.

The TTE recordings will be performed with prespecified acquisition methods by designated cardiologists [94]. The TTE recordings will include both anatomical and functional assessments of atria, valves, and ventricles as well as recording the presence or absence of pericardial effusion, thrombus, and aneurysm. Moreover, the echocardiographic raw data will be exported and stored for further analyses, such as strain and strain rate measurements.

In addition, the 3-month follow-up visit includes a morbidity evaluation with the use of CCS and NYHA and SF-36 questionnaires (Section 2.3.2) alongside routine clinical anamnesis and status. Moreover, the CABG cohort II will undergo ankle-brachial indexing (ABI) to record any asymptomatic peripheral artery disease (PAD).

A six-month prospective follow-up period starting from recruitment will be incorporated. Additionally, a six-month retrospective evaluation will be performed preceding the moment of recruitment. Hospital admission rates with primary cause(s), medication changes, determination of Major Adverse Cardiac and Cerebrovascular Events (MACCE), and all-cause mortality for follow-up make up the parameters assessed both during retrospective evaluation and prospective follow-up.

Hospital admissions regarded as cardiovascular-based will be recorded using the International Statistical Classification of Diseases and Related Health Problems (ICD-10). The IHD-EPITRAN study will use a modified MACCE definition adopted from the ITALIC trial [95] with a composite primary outcome including cardiovascular death, MI, acute revascularization, stroke, transient ischemic attack (TIA), major bleeding (The Bleeding Academic Research Consortium [BARC] classes 3–5), or other hospitalization due to ischemic cardiovascular cause [96].

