### 2.4. Power Calculations, Cohort Comparisons, Outcomes, and Data Management

The group sizes were determined with a RNAseqPS tool designed for evaluating statistical power for sequencing studies [147]. Parameter values (false discovery rate [FDR] <0.05, total number of genes for testing 20,000, predicted prognostic genes 1500 with a minimum fold change threshold of 2 for differential expression and average read counts of 10 for prognostic genes) were derived from the applicable study regarding m^6^A during hypertrophy and HF [148]. A mean dispersion value of 0.215 was doubled (0.43) and applied for the calculations. The utilized mean was based on four assessed sequencing datasets with unrelated samples and dispersions ranging from 0.15 to 0.28 [149]. Based on the power analysis, *n* = 44 per cohort generated a power of 0.95. However, the groups sizes were fixed to *n* = 50 per cohort to address possible preanalytical errors at this initial phase. Analyses with smaller sample sizes will be first performed, followed by the larger sized analyses based on the first results and methodological optimization.

Currently, there are no reports addressing either gender or age dependent changes in neither blood nor muscle tissue epitranscriptomes. As such, the produced data in the IHD-EPITRAN study will be referenced and assessed against the typical common confounding variables, such as gender, age, comorbidities, and medication. If needed, the effects will be statistically adjusted. The IHD-EPITRAN consortium (Section 2.5) includes experts with statistics expertise and knowhow.

The study cohort comparisons used to acquire the study outcomes of the IHD-EPITRAN study are presented in Figure 5 and Table 3, respectively. The project Data Management Plan (DMP) is maintained on the webpage of the IHD-EPITRAN study (www.ihd-epitran.com).

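### Secondary outcome 4.3 states the 3-month echocardiographic response in three classes although continuous functional measures are collected; within cohorts of about 50 this loses power, by an amount that can only be shown under assumptions

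*Protocol article*

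**What the plan says.** Table 3 lists secondary outcome 4 as changes in the m6A and A-to-I profiles between recruitment and 3 months. Under it, item 4.3 relates those changes to "Beneficial/adverse/no-response for therapy as measured via echocardiography at 3 months". Outcome 5 carries the item over to "profiles from the recruitment stage as in outcomes 4.2.–4.5", a range that includes 4.3. Outcomes 6 to 9 (other RNA modifications, plasma biomarkers, proteomics, leukocyte profiles) are defined by reference to outcomes 1 to 5, so they inherit it too. The neighbouring item 4.4, by contrast, speaks of biomarker levels and the changes between them.

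The table legend sets the size of each analysis: "Outcome 1 and outcomes 2–5 encase inter- and intra-cohort comparisons, respectively". Section 2.2 says the study "will recruit 50 patients in each of the four study groups", and Section 2.3.5 says "The samples will be collected twice in study cohorts I–III and once in cohort IV".

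On the measurement itself, Section 2.3.4 provides anatomical and functional assessment of atria, valves and ventricles with prespecified acquisition, and states that "the echocardiographic raw data will be exported and stored for further analyses, such as strain and strain rate measurements". The same section also includes yes/no findings: "recording the presence or absence of pericardial effusion, thrombus, and aneurysm".

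**The concern.** Strain, strain rate and similar functional measures are continuous. An endpoint in three classes treats patients just either side of a boundary as different and patients far apart within one class as equal. The cut does not appear to be forced by the design: the data for a finer analysis are collected, and item 4.4 uses levels and changes. The article gives no reason for the classes.

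The Discussion expects candidate biomarkers that reflect therapeutic responses, and 4.3 is the item in Table 3 that ties the profiles to echocardiographic response. With about 50 patients per cohort, a class can become very small: if 10% were adverse responders, that is 0.10 × 50 = 5 patients. Features that truly track functional response would then be missed more often than the data require. Because outcomes 5 to 9 refer back, one line in the table shapes several sets of analyses.

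**Working it through.** **1. The plan's own figure.** Section 2.4 gives FDR 0.05, 20,000 genes, 1,500 prognostic genes, fold change 2, mean read count 10, dispersion 0.43, and n = 44 for power 0.95.

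- Equivalent per-gene significance level: α* = 0.05 × 1,500 × 0.95 / [(20,000 − 1,500) × 0.95] = 71.25 / 17,575 = 0.00405.
- Wald formula for a negative-binomial log fold change: n = (z₁₋α*/₂ + z₀.₉₅)² × [(1/10 + 0.43) + (1/20 + 0.43)] / (ln 2)² = (2.874 + 1.645)² × 1.01 / 0.4805 ≈ 42.9.
- Power at n = 44 is 0.956 by this formula and 0.954 by an exact negative-binomial test.

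The stated n = 44 therefore reproduces. It concerns a two-group comparison at fold change 2 and says nothing about outcome 4.3, for which the article gives no power.

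**2. Inputs for outcome 4.3.** From the article: n = 50 per cohort, intra-cohort analysis, three classes. Not in the article, hence assumed:

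- a linear association with correlation r between a profile feature and the echo measure, bivariate normal;
- class shares from equal thirds to 10/80/10;
- a three-class test, either an ordered trend or an unordered one-way ANOVA;
- a per-test level of 0.05, or α* = 0.00405 borrowed from step 1.

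**3. Reference point.** Choose r so that the continuous analysis has about 80% power: r = tanh[(z₁₋α/₂ + 0.842) / √(50 − 3)].

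- α = 0.05: r = tanh(2.802 / 6.856) = 0.39.
- α* = 0.00405: r = tanh(3.716 / 6.856) = 0.49.

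**4. Simulation at n = 50, 10,000 runs per setting.** The same simulated data are analysed on the full scale and after cutting into three classes. Shares are adverse / no response / beneficial.

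| α | Class shares (%) | Continuous | Three-class trend | Three-class ANOVA | Loss (points) |
|---|---|---|---|---|---|
| 0.05 | 33/33/33 | 0.81 | 0.72 | 0.61 | 10 / 20 |
| 0.05 | 20/40/40 | 0.80 | 0.70 | 0.59 | 10 / 21 |
| 0.05 | 10/60/30 | 0.80 | 0.67 | 0.56 | 13 / 24 |
| 0.05 | 10/80/10 | 0.81 | 0.58 | 0.47 | 23 / 34 |
| 0.00405 | 33/33/33 | 0.81 | 0.66 | 0.52 | 15 / 29 |
| 0.00405 | 20/40/40 | 0.80 | 0.65 | 0.53 | 15 / 28 |
| 0.00405 | 10/60/30 | 0.80 | 0.62 | 0.49 | 18 / 31 |
| 0.00405 | 10/80/10 | 0.81 | 0.48 | 0.36 | 33 / 45 |

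Losses are taken before rounding, so they can differ by a point from the rounded columns.

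**5. How far the size depends on the assumptions.**

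- Stronger association: with continuous power at 0.95, the loss over the same class shares is 6 to 28 points at α = 0.05 and 8 to 40 at α*. At r = 0.60 and α = 0.05, the trend test on equal thirds loses only about 1 point, because both analyses are close to full power.
- Weak association: at r = 0.30 and α*, continuous power is only about 22% and the loss is about 7 to 15 points.
- Over r = 0.3 to 0.6 and the class shares in the table, the loss runs from about 1 to 45 points. A more lopsided split of 5/85/10 extends the top of the range to about 53.

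The direction was the same in every setting tried.

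**The case against.** The strongest reply is that 4.3 is one line in a condensed outcome table. It names no parameter, cut-point or model, and those may stand in the full protocol or analysis plan, so their absence is no fault. That is right, and the point does not rest on it. It rests on the outcome as stated, which is in classes and which an analysis plan would normally implement.

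A reader might infer that the article rules out a continuous analysis. It does not: raw echo data are kept, and the Expected Results section foresees using them to interpret the epitranscriptomic data. That makes the correction easy but leaves the wording of 4.3 as it is.

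A reader might also infer that all the echo measurements are continuous. Section 2.3.4 shows otherwise: effusion, thrombus and aneurysm are recorded as present or absent, and a clinical judgement of response across several parameters may have no single continuous equivalent. The loss applies to continuous measures only.

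A reader might take the 10 to 45 points as a fixed cost of this plan. The documents do not support that, because r, the class shares and the test are all assumed. The linear model also favours the continuous test; an unordered comparison of three groups could pick up a non-monotone relation that a linear test misses. Finally, the simulation compared a continuous with a classed echo variable and did not evaluate the baseline-adjusted analysis proposed below.

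Nor is 4.3 the plan's sole look at response to therapy. Items 4.1.1 to 4.1.3 address therapy effects and remodelling, and outcomes 5 to 9 repeat the question in other data.

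**Conclusion.** The point holds in a limited form. Outcome 4.3 is stated as three response classes and outcomes 5 to 9 inherit it, while continuous functional measures are already collected. For such measures, classing loses power within a cohort of about 50. If the association is linear and the continuous analysis would have about 80% power, the loss is roughly 10 to 45 points for class shares from equal thirds to 10/80/10. It shrinks when the association is strong or very weak.

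This is a cheap improvement to a secondary outcome in a discovery study, not a flaw that threatens it. The primary outcomes and the sample-size calculation stand.

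**What to change.** Reword 4.3 along these lines: *association with echocardiographic response at 3 months, with the main analysis on the continuous 3-month value of a functional echo measure named in advance for each cohort, adjusted for its recruitment or pre-treatment value where recorded; the classes beneficial, adverse and no response are reported as a descriptive or supportive summary.* Outcomes 5 to 9 then inherit the change by reference.

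The cost is one line in Table 3, a matching entry in the analysis plan, and agreement on one measure per cohort, since the therapies in cohorts I to III act differently. No further patients or measurements are needed. The small downside is that the result is expressed per unit of the echo measure, which is less direct for clinicians than a responder class. Keeping the classes as a summary meets that need.
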